## Background

Major depressive disorder (MDD) is one of the most prevalent psychiatric disorders characterized by high relapse and/or recurrence rates. Relapse is defined as ‘a return of symptoms satisfying the full syndrome criteria for an episode that occurs during the period of remission, but before recovery’, where remission is a period in which the individual no longer meets syndrome criteria for the disorder and has no more than minimal symptoms, and recovery is being in remission for 6 months or longer; recurrence is ’ the appearance of a new episode of MDD occurring during recovery’ [1]. In a large prospective study, a recurrence rate of 85% was observed in outpatients with MDD during a follow-up period of 15 years [2]. Furthermore, the recurrence risk has been shown to increase with 16% after each successive episode [3]. Given the high psychological as well as social and economic burden associated with MDD, relapse/recurrence prevention is extremely important. The most commonly used strategy to prevent relapse/recurrence is maintenance treatment with antidepressant medication (mADM). International guidelines recommend that patients with recurrent MDD should continue mADM for at least two years after remission [4]. A meta-analysis showed that mADM reduces relapse/recurrence rates significantly compared to placebo (18% versus 41%) based on 31 randomized controlled trials with follow-up periods ranging from 6 to 36 months [5]. However, despite the established effectiveness of mADM as a preventive strategy, it has several disadvantages. First, many patients are unwilling to continue mADM for a longer period [6] and adherence is typically low [7]. Second, many patients experience disturbing side effects [8]. Moreover, many patients prefer psychological over pharmacological treatment [9]. Psychotherapeutic approaches also seem to have long-term beneficial effects, whereas effects of mADM cease after discontinuation [10]. To address the need for psychological interventions targeting relapse prevention, Segal, Williams and Teasdale developed Mindfulness-Based Cognitive Therapy (MBCT) [11]. The aim of MBCT is not to change or eliminate depressive symptoms, but rather to relate to them in a different way, i.e. with a more accepting, mild attitude. The rationale behind the MBCT program is based on an empirically supported, theoretical framework suggesting that patients with recurrent depression become more vulnerable to developing depression as cognitive reactivity increases (for a review see [12]). Cognitive reactivity refers to negative modes of thinking and behaving that are reactivated in periods of stress or low mood. It is suggested that these (automatic) negative reactions in turn, lead to a further lowering of mood, eventually turning into a depressive relapse/recurrence [13]. Cognitive reactivity is strongly related to rumination, which refers to recurrently thinking about one’s depressive symptoms and their possible causes and implications. Rumination is thought to be an important cognitive vulnerability factor for both onset and relapse/recurrence in depression [14,15]. MBCT is targeted at recognizing these cognitive and behavioral reactions to low mood or other stressful situations, and to observe these reactions with acceptance and kindness and from a wider, decentered perspective. Indeed, there is evidence that MBCT diminishes the ‘toxic’ relationship between post-treatment cognitive reactivity and depressive relapse [16] and that decreased rumination mediates the effects of MBCT [17]. Unlike cognitive reactivity and rumination, self-compassion seems to be a beneficial factor that is protective against depression. Self-compassion can be described as a combination of (a) self-kindness - being kind and understanding toward oneself in instances of pain or failure, (b) common humanity - perceiving one’s experiences as part of the larger human experience, and (c) mindfulness - holding painful thoughts and feelings in balanced awareness [18]. Evidence suggests that both self-compassion and mindfulness skills mediate the effect of MBCT on relapse/recurrence [16]. Three randomized controlled trials (RCTs) have shown that MBCT in addition to treatment as usual (TAU) significantly reduced the relapse/recurrence risk compared with TAU alone, over a period of 14 months [19-21]. In the first two trials [19,20], beneficial effects of MBCT were seen in patients with three or more past episodes, whereas no difference in relapse/recurrence percentages between MBCT and TAU was observed in patients with two past episodes (but see [22] for positive effects of MBCT in patients with one or two past episodes). Another trial has shown that MBCT’s prophylactic effect is at least equal to mADM for patients with three or more past episodes [23]. This latter finding may specifically apply to patients whose remission is unstable [24]. There is also evidence that MBCT might reduce subthreshold depressive symptoms, an important risk factor for relapse/recurrence, in patients remitted from MDD [22] and patients with current MDD [17]. A recent meta-analysis [25] showed that the overall risk ratio for relapse/recurrence after MBCT is 0.66 (a relative risk reduction of 34%) compared with TAU or placebo indicating that MBCT is indeed an effective prophylactic intervention for patients with recurrent MDD in remission. However, the prophylactic effectiveness of the *combination* of MBCT plus mADM has not yet been compared with either mADM or MBCT on their own. More specifically, MBCT has not been studied as an additional treatment in patients continuing mADM, rather than TAU, to prevent relapse/recurrence. Also, up to now we do not know if continuing mADM after MBCT has additional benefits over withdrawing from mADM after MBCT. As more and more MBCT courses are available, answering these specific questions becomes increasingly important for patients and clinicians in order to find the optimal strategy to prevent relapse/recurrence. The current study is designed to answer these questions.

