
### Aims

The purpose of the ‘MOMENT’ study is twofold using two separate but connected RCTs to answer the following questions: 1) “In patients who are in remission of depression, who are being prescribed mADM and who are reluctant to discontinue medical treatment, is MBCT when given as an add-on therapy superior to the continuation of medical treatment alone?” (mADM versus mADM + MBCT) and 2) “In patients who are in remission of depression who are being prescribed mADM and who are willing to try MBCT and not unwilling to discontinue medical treatment, is MBCT with a tapering off regimen of the medical treatment not inferior to MBCT in combination with continued medical treatment?” (MBCT versus mADM + MBCT). Our primary outcome is relapse and/or recurrence. Thus, the results of this study will inform patients with MDD and mental health professionals about the relapse and recurrence risks associated with the different treatment options given a certain treatment preference, and will support decision making processes regarding these options. In addition to these primary aims, we intend to examine; 3) the effect of mADM versus mADM + MBCT on the time to, number, duration and severity of relapse/recurrence, quality of life, and personality; 4) the effect of MBCT versus mADM + MBCT on the time to number, duration and severity of relapse/recurrence, quality of life, and personality; 5) several process variables such as MBCT adherence, rumination, cognitive reactivity, mindfulness skills, and self-compassion as possible mechanisms underlying the clinical effectiveness of MBCT; 6) the cost-effectiveness of mADM versus mADM + MBCT and 7) the cost-effectiveness of MBCT versus mADM + MBCT.

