### Sample size

#### *Trial 1: mADM* versus *mADM + MBCT*

For trial 1 we need to recruit 96 participants (n = 48 per group) in order to demonstrate a difference of 25% in relapse/recurrence rates between mADM and mADM + MBCT, with a power of 80% (alpha 0.05, one-sided). This calculation is based on earlier studies reporting relapse/recurrence percentages of 60% in the mADM group [23] and approximately 38% in the MBCT plus TAU group [25]. Because our trial investigates MBCT plus mADM rather than MBCT plus TAU, we expect an even lower relapse/recurrence percentage (about 35%) in the combination group. Our expected difference is therefore 60% (mADM) minus 35% (mADM + MBCT) resulting in 25%.

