#### *Trial 2: MBCT* versus *mADM + MBCT*

The sample size of trial 2 is based on the principle of non-inferiority. According to the Draft Guidance for Industry Non-Inferiority Clinical Trials of the US Food and Drug Administration [26] non-inferiority should be demonstrated by comparing the new, experimental treatment with an established efficacious treatment. In the case of relapse prevention in depression, this established treatment is mADM. However, since a head to head comparison of MBCT with mADM is complicated due to our design, we compare MBCT with the combination therapy (mADM + MBCT). We reasoned that the difference in relapse/recurrence between MBCT and mADM + MBCT should not be larger than the difference between the established treatment (mADM) and mADM + MBCT, which is expected to be approximately 25%. Therefore, we chose a non-inferiority margin of 25%. Based on this assumption, the sample size needed in this non-inferiority trial is 280 in total (n = 140 per group) with a power of 80% (alpha 0.05, one-sided).

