### Statistical analysis

#### Primary analyses

Our primary analyses will be based on intention-to-treat. Subsequently per-protocol analyses will be conducted. All analyses will be performed with and without covariates (i.e. the stratification factors research centre, depressive symptoms at baseline, and number of depressive episodes in the past, as well as other variables that might inadvertently be unevenly distributed over the conditions at baseline). *Trial 1: mADM* versus *mADM + MBCT.* The primary outcome measure will be relapse and/or recurrence meeting DSM-IV criteria for a major depressive episode during the 15-month study period. Relapse/recurrence rates will be compared with a Chi-square test. *Trial 2: MBCT* versus *mADM + MBCT.* The primary outcome measure will be relapse and/or recurrence meeting DSM-IV criteria for a major depressive episode during the 15-month study period. Relapse/recurrence rates will be compared with a General Linear Model using a binomial family with an identity link. We will use the confidence interval (one-sided) of the difference in relapse/recurrence between the two conditions (MBCT versus mADM + MBCT): if a difference of 25% can be excluded, then we will conclude non-inferiority of MBCT in comparison with mADM.

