## Discussion

The prevention of relapse and recurrence in depression is considered a key target in mental health care given the high prevalence of relapse/recurrence of MDD and the accompanying (societal) costs. Previous studies have shown that MBCT significantly reduces the relapse/recurrence risk as compared to treatment as usual [25], but MBCT has not yet been studied as an additional treatment to mADM. Therefore, our first trial will inform health care professionals and patients about the relapse/recurrence risks associated with MBCT in addition to mADM compared with continuing mADM on its own. However, given the large amount of patients who prefer psychological treatment instead of ADM [9] and the difficulties that many patients have with long term use of ADM [7], it seems useful to investigate whether a relatively short, group-based course such as MBCT can help patients taper off their antidepressants. Therefore, our second trial will inform patients and clinicians about the relapse/recurrence risks associated with tapering off mADM after MBCT, compared with continuing mADM after MBCT. This trial is based on non-inferiority because we reasoned that the effectiveness of MBCT on its own (i.e. discontinuing antidepressants after MBCT) should be at least comparable to the effectiveness of mADM on its own. The original study design was an RCT comparing mADM, MBCT, and mADM + MBCT. However, because of the strong treatment preferences that patients expressed during the beginning of the recruitment phase which hampered the randomization possibilities, we adapted our design. Instead of a direct comparison between the three treatment options (three-way randomization) we now allocate the patients to different RCTs based on their preference for either mADM (allocation between mADM and mADM + MBCT) or for MBCT (allocation between MBCT and mADM + MBCT). A methodological consequence of this adaptation is that we cannot directly compare MBCT to mADM because the MBCT preference group may differ from the mADM preference group with respect to known as well as unknown variables. The advantage that comes along with this design however, is an increase in the ecological validity of both trials. In our adapted design, the included patient groups probably more closely reflect the population(s) that we are interested in, since these preferences are obviously present in the population of remitted recurrently depressed adults who use mADM. Moreover, if we had continued using the original three-way randomization procedure, we would have lost all participants who were not willing to be randomly assigned to mADM only or to MBCT only, resulting in a highly selective sample with low generalizability. In summary, more detailed knowledge about the effectiveness of MBCT in addition to mADM, and about MBCT as a possible alternative to mADM is needed. Taking into account patient preferences, the MOMENT study will address these questions to support patients and clinicians in finding the optimal strategy to prevent depressive relapse and recurrence.

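### Trial 2 tests MBCT with tapering against mADM + MBCT, but its pre-set conclusion is about mADM alone, and the assumption that this needs is not stated

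*Protocol article*

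**What the plan says.** The Aims put the trial 2 question against the combination: "is MBCT with a tapering off regimen of the medical treatment not inferior to MBCT in combination with continued medical treatment". The Design section gives the same two arms. Under Primary analyses the tested quantity is again this contrast: "We will use the confidence interval (one-sided) of the difference in relapse/recurrence between the two conditions (MBCT versus mADM + MBCT"). The same sentence then fixes the conclusion: "if a difference of 25% can be excluded, then we will conclude non-inferiority of MBCT in comparison with mADM".

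The link to mADM is in the Sample size section for trial 2. It names mADM as the established treatment and says that "a head to head comparison of MBCT with mADM is complicated due to our design, we compare MBCT with the combination therapy". The margin is set so that MBCT loses no more against the combination than "the difference between the established treatment (mADM) and mADM + MBCT, which is expected to be approximately 25" per cent. That 25 is the trial 1 planning figure, 60% on mADM minus 35% on mADM + MBCT. The Discussion adds that MBCT alone should be at least comparable with mADM alone, but also that "we cannot directly compare MBCT to mADM because the MBCT preference group may differ from the mADM preference group".

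**The concern.** The interval concerns one comparator and the conclusion names another. The step between them is an assumption about D, the true relapse/recurrence rate on mADM minus that on mADM + MBCT, in patients who prefer MBCT. The decision rule carries no such condition and does not call its conclusion indirect.

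The document offers no direct evidence on D: the Background says the combination had not yet been compared with either treatment alone. Trial 1 is meant to find out whether D is above zero, but in patients reluctant to stop medication. As worded, trial 2 would declare non-inferiority to mADM whatever trial 1 showed.

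The decision at stake is whether to stop medication. A pass would be reported as MBCT holding up against maintenance medication, when the data show only that it is less than 25 points worse than the combination.

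**Working it through.** **Inputs.** Planned rates of 60% (mADM) and 35% (mADM + MBCT) and 48 per arm, from Sample size, trial 1. Margin of 25 points, 140 per arm and one-sided alpha 0.05, from Sample size, trial 2. All standard errors are unpooled normal approximations.

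**The plan's own figure.** 60 − 35 = 25 points, which is both the expected D and the margin.

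**What a pass shows.** MBCT − mADM = (MBCT − combination) − D. If the first term is shown to be below 25, then MBCT − mADM < 25 − D.

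| D (points) | Source | Bound on MBCT − mADM |
|---|---|---|
| 25 | planning assumption, 60 − 35 | 0 |
| 22 | 60 − 38, illustrative | 3 |
| 20.4 | 60 × (1 − 0.66), illustrative | 4.6 |

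The last two rows use "relapse/recurrence percentages of 60% in the mADM group [23] and approximately 38% in the MBCT plus TAU group" and "the overall risk ratio for relapse/recurrence after MBCT is 0.66 (a relative risk reduction of 34%) compared with TAU or placebo". They are sensitivity values only, because neither source compared mADM with mADM + MBCT.

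**How well D will be known.** Trial 1 at planned rates: SE = √[(0.60 × 0.40 + 0.35 × 0.65)/48] = √(0.4675/48) = 0.0987, or 9.9 points. Trial 2 with 35% in both arms: SE = √(2 × 0.2275/140) = 0.0570, or 5.7 points. Indirect MBCT − mADM contrast: SE = √(0.0987² + 0.0570²) = 0.114, or 11.4 points, twice that of the tested contrast.

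**A result that passes.** Take 70/140 (50%) on MBCT against 49/140 (35%) on the combination. The difference is 15 points, SE = √[(0.25 + 0.2275)/140] = 0.0584, and the one-sided upper limit is 15 + 1.645 × 5.84 = 24.6, below 25. Suppose trial 1 also gives its planned D of 25. The indirect estimate is 15 − 25 = −10, with SE √(9.87² + 5.84²) = 11.5 and upper limit −10 + 1.645 × 11.5 = +8.9. The estimate favours MBCT over mADM, but the upper limit does not exclude MBCT being worse. The rule would report non-inferiority to mADM without showing this.

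**Dependence of the rule on D.** Assume a combination rate of 35% and MBCT truly 5 points worse than mADM, so the true excess over the combination is d = D + 5. The chance of a pass is Φ[(25 − d)/SE − 1.645], with SE from 140 per arm. D values below 20 are assumptions chosen to show the range.

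| D | d | P(pass) |
|---|---|---|
| 25 | 30 | 0.006 |
| 15 | 20 | 0.22 |
| 10 | 15 | 0.53 |
| 5 | 10 | 0.82 |

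For the same true MBCT − mADM difference, the chance of declaring non-inferiority to mADM runs from under 1% to over 80%, depending on a quantity that trial 2 does not observe.

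**The case against.** The strongest defence is that the wording is deliberate and its rationale is disclosed. The margin was built to carry the inference about mADM, and the Discussion rules out only a direct comparison. That stands: a reader might infer that the plan flatly contradicts itself or that the trial 2 test is invalid, and the documents support neither. What remains is that the rule leaves out the condition on which the argument rests.

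It is also fair that D of at least 25 is needed only to show MBCT no worse than mADM at all. Non-inferiority normally tolerates some loss, and at D = 22 or 20.4 the bound is small. But the plan sets no margin against mADM, so nothing says what loss would be acceptable.

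Two stronger readings should be resisted.
- A reader might infer that the document's own figures put D below 25. They do not establish this: the 38% is for MBCT plus treatment as usual, the 0.66 is against treatment as usual or placebo, both cite the same meta-analysis, and the plan says why it expects a lower rate with mADM. If D exceeds 25, the stated conclusion is conservative.
- A reader might subtract trial 1's lower confidence limit for D from the 25-point limit and report a large possible disadvantage for MBCT. That stacks two limits and ignores the equally compatible high values of D. With the combined standard error at planned rates (MBCT and the combination both 35%), the indirect upper limit is −25 + 1.645 × 11.4 = −6.2, which favours MBCT.

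Finally, deleting mADM from the conclusion without comment would leave the 25-point margin with no visible justification. The fix has to deal with that.

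**Conclusion.** The point holds as a defect in the pre-set primary conclusion. The arms, test, margin arithmetic and sample size are not affected by it. A pass supports the statement that MBCT with tapering is less than 25 points worse than MBCT plus continued mADM. It supports a statement about mADM alone only as MBCT − mADM < 25 − D, with D assumed. The size therefore depends on D: the bound is zero at the planned value and a few points at the illustrative values. If D is estimated from trial 1, the indirect contrast has an SE of about 11.4 points at planned rates. That SE does not cover any difference between the preference groups, which the Discussion says may exist but which no figure in the document quantifies. None of this shows that MBCT is worse than mADM.

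**What to change.** Keep the arms, test, margin and sample size, and change the text as follows.

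1. Replace the conclusion under Primary analyses with: *Once the one-sided interval rules out a 25-point excess, the conclusion is that MBCT with tapering of mADM is non-inferior, within 25 percentage points, to MBCT plus continued mADM.*
2. Say beside it that the 25-point margin was derived from the expected difference between mADM and mADM + MBCT, so that its origin stays visible.
3. Report any statement about mADM alone only as an indirect inference, conditional on that difference holding in trial 2 patients. Values such as D = 22 and 20.4 may be shown as illustrative sensitivity values.
4. If trial 1's estimate of D is used, compute the indirect contrast with a combined standard error, not by subtracting one confidence limit from another. Repeat the Discussion's caveat that the preference groups may differ.

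The cost is a few sentences and, if wanted, one supporting calculation from data that both trials already collect. Patients, visits and treatment do not change.

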#### Secondary analyses

##### Time to relapse and number, duration and severity of relapse/recurrence

Differences in time to relapse/recurrence between mADM versus mADM + MBCT (trial 1) and between MBCT versus mADM + MBCT (trial 2) will be analyzed using a Cox Regression Proportional Hazards Model. In case of drop-out from the trial we will use the available measures and censor the participant at the time of the last assessment or informative contact. In patients suffering a relapse/recurrence during the study period we will compare the number, duration and severity of relapse/recurrence between mADM versus mADM + MBCT (trial 1) and between MBCT versus mADM + MBCT (trial 2) using a General Linear Model. We will perform additional analyses comparing different subgroups, for example patients who were in full remission at baseline (IDS-C ≤ 11) with patients who were in partial remission at baseline (IDS-C > 11) for both trials.

##### Mechanisms of change

Mediation analyses will be used to investigate the possible underlying mechanisms of change in MBCT. In accordance with other trials, these analyses will only include patients who have received an ‘adequate dose’ of MBCT, which is defined as participation in ≥ 4 of 8 MBCT sessions [16,19]. In this subsample, we will test the mediating effect of adherence to MBCT, rumination, cognitive reactivity, mindfulness skills, and self-compassion, on depressive relapse/recurrence and depression severity as outcomes, using a multiple mediation model following the approach suggested by Preacher and Hayes [57]. In addition, we will use Hierarchical Linear Modeling techniques to investigate whether change in daily attention/awareness causally influences positive and negative effect. We will perform multilevel mediational analyses following the procedure reported by Kenny, Korchmaros & Bolger [58]. We will ‘lag’ the mediator variable (daily attention/awareness) by examining whether changes on the MAAS at time *t-1* account for changes in the outcome variable (i.e. positive and negative affect) at time *t* for every MBCT session.

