**Methods/design:**

Two parallel-group, multi-center randomized controlled trials are conducted. Adult patients with a history of depression (3 or more episodes), currently either in full or partial remission and currently treated with mADM (6 months or longer) are recruited. In the first trial, we compare mADM on its own with mADM plus MBCT. In the second trial, we compare MBCT on its own, including tapering of mADM, with mADM plus MBCT. Follow-up assessments are administered at 3-month intervals for 15 months. Primary outcome is relapse/recurrence. Secondary outcomes are time to, duration and severity of relapse/recurrence, quality of life, personality, several process variables, and incremental cost-effectiveness ratio.

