### Interventions

#### mADM

All study participants are on a stable dose of mADM for at least 6 months prior to enrollment (inclusion criterion). In the mADM group participants continue their use of mADM during the study period of 15 months. After randomization, participants are seen by a study psychiatrist for a review of their mADM. For optimization of mADM, psychiatrists taking part in the study use a protocol based on national [32] and international [33] guidelines, made applicable for the MOMENT study by two experts in pharmacological treatment of MDD ([name]). Switching or augmenting medication is allowed between T0 and T1, and recommendations to manage side effects are provided. Compliance with mADM is measured prospectively during the whole study period using a daily calendar. Participants in the mADM condition are invited to take part in the MBCT training after the study period if they are interested.

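### The mediation analysis is limited to patients who attended at least 4 of 8 MBCT sessions, so it has no arm without MBCT and cannot estimate mediation of the MBCT effect

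*Protocol article*

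**What the plan says.** Under Aims, the fifth aim of the protocol article is to examine "several process variables such as MBCT adherence, rumination, cognitive reactivity, mindfulness skills, and self-compassion as possible mechanisms underlying the clinical effectiveness of MBCT".

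The section Mechanisms of change fixes the analysis set: "these analyses will only include patients who have received an ‘adequate dose’ of MBCT". The threshold for an adequate dose is attendance at four or more of the eight sessions. The restriction is then repeated for the model itself: "In this subsample, we will test the mediating effect of adherence to MBCT, rumination, cognitive reactivity, mindfulness skills, and self-compassion". The outcomes are depressive relapse/recurrence and depression severity, and the method is a multiple mediation model. No exposure variable is named, and nothing says that control patients are kept.

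On the arms, the abstract states: "In the first trial, we compare mADM on its own with mADM plus MBCT". The mADM part of Interventions adds: "Participants in the mADM condition are invited to take part in the MBCT training after the study period if they are interested". In trial 2 both arms take the MBCT course; they differ in whether mADM is tapered or continued.

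Table 1 schedules rumination (RRS), cognitive reactivity (LEIDS), mindfulness skills (FFMQ) and self-compassion (SCS) at T0, T1 and T5, with no restriction by arm. It schedules the IDS-C at T0 and at T1 to T5.

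**The concern.** Mediation of a treatment effect needs a contrast in that treatment. The model must show that the treatment moves the mediator and that the mediator in turn moves the outcome. If every analysed patient has had MBCT, the first link has no comparison.

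Patients who ruminate less after MBCT may relapse less often whether or not MBCT caused the reduction. A correlation between mediator and relapse among attenders would look the same in both cases. Reported as mediation, it could present a prognostic marker as a mechanism of MBCT.

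Two further features add to this. Attendance is a self-selected variable that arises after randomisation. And MBCT adherence is listed among the mediators, although it measures exposure and has no counterpart in an arm without MBCT.

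**Working it through.** **Inputs.** Trial 1: 96 patients, 48 per group, with expected rates of 60% and 35%, 80% power and one-sided alpha 0.05. Trial 2: 280 patients, 140 per group. Analysis set: at least 4 of 8 sessions. The arm definitions are as given above.

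**Step 1: the plan's own figure, for context.** For two proportions with pooled variance and no continuity correction,

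n = [1.645·√(2·0.475·0.525) + 0.842·√(0.60·0.40 + 0.35·0.65)]² / 0.25² ≈ 48.3, so 49 per arm.

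With 48 per arm the power is 0.798. The stated 96 is reproduced to within 2 patients. The point does not depend on this figure.

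**Step 2: who can meet the rule.**

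| Group | Receives MBCT in the study | Can attend ≥ 4 sessions |
|---|---|---|
| Trial 1, mADM | no (offered afterwards) | 0 of 48 |
| Trial 1, mADM + MBCT | yes | at most 48 of 48 |
| Trial 2, MBCT with tapering | yes | at most 140 of 140 |
| Trial 2, mADM + MBCT | yes | at most 140 of 140 |

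Pooling the trials would not help: at most 48 + 280 = 328 patients, all of them MBCT recipients.

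**Step 3: what the model can estimate.** Let X be MBCT (1) or no MBCT (0), M the mediator and Y the outcome. The path from X to M is a = Cov(X, M) / Var(X), and the indirect effect is a·b, where b is the slope of Y on M given X. In all of trial 1, half the patients have X = 1, so Var(X) = 0.5 × 0.5 = 0.25. In the subset every patient has X = 1, so Var(X) = 1 × 0 = 0. Then a, a·b and the total effect of MBCT are undefined whatever the number of patients.

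**Step 4: what the subset would show instead.** A linear single-mediator model was simulated with 200,000 patients per scenario. About 76% of MBCT patients were attenders, which is an assumption of the simulation.

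| Scenario | True a | True b | Estimated a, all patients | Slope of Y on M, all patients | Slope of Y on M, attenders only |
|---|---|---|---|---|---|
| MBCT moves the mediator | 0.5 | −0.5 | 0.50 | −0.49 | −0.50 |
| MBCT does not move it | 0 | −0.5 | 0.00 | −0.50 | −0.50 |
| No mediation, unmeasured confounder of M and Y | 0 | 0 | 0.00 | −0.33 | −0.30 |

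In the first row the true indirect effect is 0.5 × (−0.5) = −0.25; in the second it is 0. The attenders give the same slope in both. The full sample separates them through a. The third row limits the remedy: with an unmeasured common cause, b is biased even when the control arm is present.

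**The case against.** The best defence is that the rule was meant only to drop under-dosed patients within the MBCT arms. The section says it follows other trials, and Table 1 collects the mediators in every arm. That intent is possible, and the cited trials are not at hand. But the text restricts the set twice and makes no exception for controls, so the wording needs correcting even on this reading. Nor is this detail left to an analysis plan: the analysis set is stated here.

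Several objections to a wider criticism stand.

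- *A reader might infer that aim 5 cannot be addressed at all.* The documents do not support that. The aim is to examine possible mechanisms and includes MBCT adherence. Attendance from 4 to 8 sessions and daily practice on the calendar vary among recipients and can be related to skills and relapse, though only observationally. The planned lagged analysis of daily attention and affect is within-person and needs no control arm; it does not concern relapse.
- *A reader might infer that the subset contains no randomised exposure.* No exposure is named, and in trial 2 the allocated arm still varies. Mediation of tapering versus continuing mADM can be estimated there, subject to selection on attendance. The zero variance applies to MBCT yes or no.
- *A reader might infer that relapses before T1 will be attributed to mediators measured later.* The section fixes neither the mediator time point nor how early relapses are handled, and IDS-C at T2 to T5 does follow T1. The time order should be stated; the article does not show that it is reversed.

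**Conclusion.** The point holds for mediation of the MBCT effect. As written, the only comparison of MBCT with no MBCT is lost: trial 1 goes from 48 versus 48 planned patients to 0 versus at most 48, and the indirect effect of MBCT on relapse or severity is not estimable. This rests on the literal reading of the attendance rule and on the mADM arm having no MBCT during the 15-month study. It does not depend on attendance rates or effect sizes.

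Exploratory information on aim 5 remains within MBCT recipients, as does a taper-versus-continue question in trial 2. Neither is mediation of the MBCT effect. This is a secondary analysis, and the primary conclusions of both trials are unaffected. It should be corrected because the stated rule cannot deliver the stated analysis and the repair is cheap.

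**What to change.** In Mechanisms of change:

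1. **Main analysis of the MBCT effect.** Use trial 1, all randomised patients in both arms, with allocated arm as exposure. Mediators are the T1 values of rumination, cognitive reactivity, mindfulness skills and self-compassion, adjusted for their T0 values, the minimisation factors and other baseline prognostic variables such as baseline IDS-C. Outcomes follow T1: relapse/recurrence after T1, and IDS-C at T2 to T5.
2. **Attendance subset.** Keep the rule of at least 4 sessions only as a sensitivity analysis. Apply it to the MBCT arm, retain all mADM controls, and label the comparison non-randomised, because attenders are still self-selected.
3. **MBCT adherence.** Remove it from the mediators and analyse it as an exploratory dose-response within MBCT recipients.
4. **Trial 2.** Describe any mediation result as concerning tapering versus continuing mADM, not MBCT.

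**Cost.** The change is to analysis wording; the questionnaires are already scheduled at T0 and T1 without restriction by arm. There are three downsides. Fewer relapse events remain after T1. The relapse analysis conditions on being relapse-free at T1, which treatment may affect. And confounding between mediator and outcome can persist after adjustment, as the third simulated scenario shows. Restoring the control arm is therefore necessary but not sufficient, and the results should be reported as exploratory.
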